## Methods

### Study design

A randomised, double-blind, placebo-controlled trial with two parallel arms: dexamethasone versus placebo during the first 6 weeks of treatment. This multicentre study will recruit patients who offer informed consent across Asia and Africa, in Malawi, Uganda, Laos, Thailand, Indonesia, and Vietnam. The study is pragmatic, designed to maintain relevance through trialing adjuvant treatment with dexamethasone in the context of the best standard of locally available care.

### Dexamethasone-treatment dose

Dexamethasone will be given in a reducing dose according to body weight (Table 4):

**Table 4 Tab4:** **Dexamethasone-reducing regimen**

Period	Dexamethasone Dose	Timing
Week 1	0.3 mg/kg iv	Once daily
Week 2	0.2 mg/kg iv	Once daily
Week 3	0.1 mg/kg po	Once daily
Week 4	3.0 mg total/day po	Once daily
Week 5	2.0 mg total/day po	Once daily
Week 6	1.0 mg total/day po	Once daily
Week 7 onwards	Stops	

This dose is identical to the dose used in patients with Grade 1 tuberculous meningitis and has been shown to have a low rate of side effects [10]. Dexamethasone/placebo will be administered intravenously, during the period of intravenous antifungal treatment, and orally once antifungal treatment is administered orally. Treatment will be weight-dosed to the nearest half milligram. With the exception of the first dose, which should be given with the first dose of antifungal therapy, dexamethasone should be given in the morning.

## Study population

All HIV-infected adult patients with a diagnosis of CM presenting to the study centres will be eligible to enter the study, subject to meeting the inclusion/exclusion criteria and giving informed consent.

### Trial location

The study will recruit patients at sites in Vietnam, Indonesia, Thailand, Laos, Uganda, and Malawi.

### Inclusion criteria

Age ≥18 yearsHIV antibody positiveCryptococcal meningitis defined as a syndrome consistent with CM and one or more of ○ positive CSF India ink (budding encapsulated yeasts),○ *C. neoformans* cultured from CSF or blood,○ positive cryptococcal antigen Lateral Flow Antigen Test (LFA) in CSF

Informed consent to participate given by patient or acceptable representative

### Exclusion criteria

PregnancyActive gastrointestinal bleeding (defined as vomiting blood or melena stool in the previous week)Currently receiving treatment for CM and having received ≥1 week of anti-CM therapyKnown allergy to dexamethasoneCurrent steroid use defined as currently receiving the equivalent of prednisolone 40 mg/day or morecurrently receiving steroid therapy (any dose) for more than 3 weeks (except topical steroids, which are permitted)Concurrent condition for which corticosteroids are indicated because of proven benefit (such as severe *Pneumocystis* pneumonia (pO_2_ < 70 mm Hg) or tuberculous meningitis)Renal failure (defined as creatinine >3 × ULN, despite adequate hydration)

## Study procedures

### Recruitment

The target population for study screening is any patient known or suspected to have CM. To enter the study, patients must be confirmed to have CM according to the definition in the inclusion criteria. Screening procedures will adapt to the standard of care of each setting to ensure that study-related procedures are performed only after informed consent has been obtained. According to the clinical care of the treating hospital, patients suspected of having CM will undergoan IMMY lateral-flow cryptococcal antigen test (LFA) on serum or plasma,AND/ORblood culture for *Cryptococcus*AND/ORa lumbar puncture with an IMMY lateral-flow cryptococcal antigen test, and/or microscopic examination of CSF, and/or culture of CSF.When the results of the IMMY lateral-flow test (plasma, serum, or CSF), or CSF microscopy, or blood or CSF culture are available, study staff may consider whether the patient should be approached regarding the study. Only patients 18 years or older who are not known to be pregnant and who have evidence of cryptococcal disease from one of the specified tests will be approached.

A member of study staff will invite the patient to discuss the details of the study. If the patient is judged by the staff to be unfit or unable to give informed consent, an acceptable representative will act on the patient’s behalf for the following procedures. The study staff will give the patient/representative a copy of the informed-consent form and explain the details of the study, including the study procedures, risks and benefits, financial and confidentiality considerations, treatment alternatives, and how to obtain more information. The study staff will invite the patient/representative to ask questions and will endeavour to ensure that she or he understands the information given. The study staff will then ask the patient/representative to consider study participation. Those who refuse consent will be treated as per the best available standard care and will not have any study-related procedures performed.

Those who consent to the study will sign and date two copies of the informed-consent form. The study staff will also sign and date the two copies.

If the patient/representative is illiterate, a witness who is not a member of the study staff will be present during the informed-consent discussion. The informed-consent form will be read to the patient/representative in the presence of the witness. If the patient/representative agrees to participate, the form will be signed and dated by the witness.

Consenting patients will be screened for eligibility.

### Screening

Only patients who are 18 years or older, who are not known to be pregnant, and who have at least one of positive CSF or blood/serum LFA test, positive blood or CSF culture, or positive CSF microscopy will be consented. Consenting patients will undergo the following screening procedures/tests. In the case of an unconscious patient, information will be obtained from a knowledgeable relative or caregiver.Medical history will be taken, including: (a) signs and symptoms consistent with cryptococcal meningitis, (b) allergy to dexamethasone, and (c) history of corticosteroid use and antifungal therapy.Patient will be checked for signs of active gastrointestinal bleeding.All women of child-bearing age will have a urine or blood pregnancy test.Creatinine levelHIV status will be confirmed from clinical history or testing as per standard of care.A lumbar puncture will be performed on all patients to obtain CSF. CSF will be tested by: (a) India ink stain or equivalent, (b) culture, and (c) lateral-flow cryptococcal antigen test. Cultured isolates will be stored for subsequent studies.If a lumbar puncture was done recently (within 48 hours) for clinical care, and volume of fresh CSF remains available for these tests (stored according to established SOPs), the lumbar puncture need not be repeated.If the patient underwent a recent lumbar puncture, an additional puncture will be performed (provided no contraindications exist) if any of the following are true: (a) uncertainty exists regarding the microbiologic diagnosis, (b) increased intracranial pressure is suspected, (c) the previous puncture was >2 days before, and no effective treatment has been given, and (d) it is required for standard care. If none of these is true or if the patient refuses further lumbar puncture, the patients may be randomised without additional lumbar puncture, provided they are eligible for the study.If the lumbar puncture was not recent, it will be repeated (provided no contraindications exist) to confirm the diagnosis, and to determine CSF pressure and fungal burden.

All lumbar punctures require verbal or written consent according to local standard clinical practice. Failure to consent according to local practice is a contraindication to the procedure.

When all inclusion and exclusion criteria are verified, eligible patients will be randomised to treatment.Patients who are determined to be ineligible will be withdrawn from the study, and the reason recorded. Patients withdrawn from the study will be treated according to the best available standard care. Screening flow is illustrated in Figure 3.

**Figure 3 Fig3:**
[figure not shown]
**Screening-study flow diagram.**

The number of patients who do meet inclusion/exclusion criteria, but are not enrolled in the study will be recorded.

### Randomisation

Randomisation will be 1:1 to either dexamethasone or identical placebo. Patients will be stratified by hospital of enrolment. Enrolment logs specific to each site will be used to assign patients to the next available sequential number. The assigned number will correspond to a blinded, sealed, treatment pack containing dexamethasone for injection and dexamethasone tablets, or visually identical placebos. Treatment packs will be prepared centrally by an unblinded study pharmacist and distributed to the sites in batches, as required. Only central study pharmacists who hold the master randomisation list will know the contents of each pack. This list will be accessed only in the case of emergency unblinding, authorised by an investigator or designee, as per standard operating procedures. At each site we will use block randomisation with variable block lengths of size 4 (with probability 0.75) or 6 (with probability 0.25), respectively. Stratification by site will minimise the effect of any differences in patient or health care characteristics by ensuring that nearly equal numbers of patients receive either of the two treatment arms at each site. Drug appearance and administration schedules will be identical to maintain blinding amongst the attending physicians and nurses.

## Patient management

### Initial evaluation

On admission, all patients will have a full clinical assessment and examination.

Study-entry laboratory tests will be performed as per the study schedule in section Treatment of CM.

A baseline chest radiograph will be performed. A CT or MRI brain scan will be performed if evidence is found of increased intracranial pressure or focal neurologic abnormalities according to local practice and resources.

### Other treatment

#### Antifungal treatment

All patients will receive antifungal treatment consisting of 2 weeks of intravenous amphotericin B, 1 mg/kg/day, combined with high-dose fluconazole (800 mg/day), followed by fluconazole 800 mg/day for 8 weeks (10 weeks in total; see Appendix 4 and Appendix 5). This is locally feasible and consistent with recent guidelines [3, 4]. After the 10-week period of therapy, all patients, provided they have responded to treatment, will receive long-term secondary prophylaxis with fluconazole, 200 mg/day. Modification of antifungal therapy will be made according to the patient’s needs and the judgment of the attending physician. Any changes to antifungal therapy will be recorded in the case-record form. The cost of antifungal treatment (including secondary prophylaxis until 6 months after randomisation) will be covered by existing local financial support or trial finances.

#### Antiretroviral therapy

All patients must to be referred to local HIV services as soon as practicable, preferably while still admitted to hospital, to ensure that they have access to locally available HIV services, including counselling and ARVs.

It is not clear when antiretroviral therapy should be started in CM. Large studies are currently under way to answer this question. Early initiation may offer faster immune reconstitution benefiting survival, or may increase the risk of IRIS and drug toxicities, adversely affecting survival. In the absence of reliable data, most physicians would recommend starting ARVs after 4 weeks of antifungal treatment, provided the patient has made a good response. The date that ARVs are started (or stopped) in patients in the study will be recorded.

#### Opportunistic infection prophylaxis

Most patients will be profoundly immunosuppressed and should receive prophylactic therapy against other opportunistic infections, such as daily trimethoprim-sulfamethoxazole, in accordance with local guidelines and practices.

### Hospital admission

Intravenous amphotericin B is administered for 14 days, necessitating hospital admission during this period.

### Clinical monitoring

Patients will have daily GCS and review, as per standard care, until discharge from hospital. The decision to discharge patients from the hospital is at the attending physician’s discretion and is based on the clinical status of the patient. After discharge, patients will be seen weekly until 4 weeks, at 6 weeks, and at 10 weeks. If the exact visit day is not feasible, scheduled visits can occur at up to 5 days after the stipulated time to account for weekend and holidays (for example, the 4-week review should occur on day 28 to 33 after randomisation, and week 10 visit on day 70 through 75). Patients will be monitored closely for

Death: the date of death and cause will be recordedNew neurologic events (onset of new focal neurologic signs or decrease in Glasgow coma scale score of ≥2 points for ≥2 days, after >7 days clinical stability or improvement after randomisation)Drug-related adverse eventsNew or recurrent AIDS-defining illnesses (see Table 5)

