#### Time to new neurologic event or death until 10 weeks

A neurologic event is defined as a decrease in Glasgow coma scale score by ≥2 points for ≥2 days from the highest previously recorded Glasgow coma scale score (including baseline) or the occurrence of any of the following adverse events: cerebellar symptoms, coma, hemiplegia, paraplegia, seizures, cerebral herniation, new-onset blindness or deafness, or cranial nerve palsy.

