##### Adverse events

The frequency of serious and grade 3 and 4 adverse reactions as well as the frequency of specific adverse events will be summarised (both in terms of the total number of events as well as the number of patients with at least one event). The proportion of patients with at least one such event (overall and for each specific event separately) will be summarised and (informally) compared between the two treatment groups based on the Fisher Exact test.

**The rate of IRIS and the rate of relapse** (defined as antifungal treatment intensification or re-treatment) will be modelled with cause-specific proportional hazards models stratified by continent, taking into account the competing risk of prior death. Cumulative incidence functions for the competing events will also be calculated and displayed by treatment arm. Secondary time-to-event end points (time to new AIDS-defining illness or death and time to new neurologic event or death) will be analysed with Kaplan-Meier curves and Cox regression models, as described for the primary end point expressed earlier. The proportion of patients with blindness or visual deficit will be compared between the two arms with a logistic regression (as for the proportion of patients with good disability described earlier).

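### The secondary end point of new neurologic event or death has two conflicting event definitions: the end-point section counts from randomisation, while the monitoring section requires more than 7 days of stability first

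*Protocol article*

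**What the plan says.** The section *Time to new neurologic event or death until 10 weeks* gives the formal end-point definition: "A neurologic event is defined as a decrease in Glasgow coma scale score by ≥2 points for ≥2 days from the highest previously recorded" score, with baseline among the eligible reference scores. The alternative criterion is "the occurrence of any of the following adverse events: cerebellar symptoms, coma, hemiplegia, paraplegia, seizures", a list that goes on to cerebral herniation, new blindness or deafness, and cranial nerve palsy. It sets no lead-in period and no severity threshold.

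The section *Clinical monitoring* lists what patients are to be watched for. Its entry for new neurologic events covers the onset of new focal signs or a "decrease in Glasgow coma scale score of ≥2 points for ≥2 days, after >7 days clinical stability or improvement after randomisation". It gives no reference score for the fall and does not name seizures or coma.

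The analysis text on secondary end points names "time to new AIDS-defining illness or death and time to new neurologic event or death" for Kaplan-Meier curves and Cox models of the kind used for the primary end point. It does not say which event definition applies, and neither definition refers to the other.

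**The concern.** One analysed end point should have one event rule, used both by the staff who capture events and by the statistician who counts them. Here a sustained GCS fall starting on day 3 is an event under the end-point section and cannot be one under the monitoring section. If sites flag events by the monitoring wording, the data assembled for this end point may not match the definition to be analysed. If the choice is left until analysis, there is avoidable discretion over a secondary result.

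The stretch in dispute is not a neutral one. Week 1 carries the highest study-drug dose in Table 4, and the rationale rests partly on reducing cerebral oedema and intracranial pressure. Deaths count under either rule, so the two versions of the composite differ only in its non-fatal part.

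**Working it through.** No sample size, power or event count enters this point, and the plan states no figure to reproduce. The check sets the two texts side by side, followed by one line of timeline arithmetic.

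| Feature | End-point section | Clinical monitoring section |
|---|---|---|
| GCS fall | At least 2 points for at least 2 days | Same size and duration |
| Reference score | Highest earlier score, baseline included | Not stated |
| Stability required first | None | More than 7 days of stability or improvement after randomisation |
| Other events | Named list, including coma and seizures | New focal signs only |
| Severity threshold | None | None |

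**1. Time closed to GCS events.** The window is 10 weeks, so 10 × 7 = 70 days. Under the monitoring wording no GCS fall can qualify until more than 7 days of stability or improvement have passed. At least 7 of 70 days are therefore closed: 7 / 70 = 10% of the window. This is a minimum, because a patient who stabilises late is closed for longer, and one who never has more than 7 stable days is closed throughout.

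**2. Focal signs.** The stability clause follows a comma after both alternatives. It may govern both or only the GCS fall. It clearly applies to GCS falls; its reach over focal signs is ambiguous.

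**3. Events outside the monitoring wording at any time.** A seizure or coma without a focal sign is on the end-point list but is not named in the monitoring entry. Coma might qualify there through a GCS fall, subject to the stability clause.

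**4. What other data would still capture.**
- *GCS falls.* "Patients will have daily GCS and review, as per standard care, until discharge from hospital", and "Intravenous amphotericin B is administered for 14 days, necessitating hospital admission during this period". The first week therefore lies inside a period of daily scoring. Early falls can be derived afterwards, provided the individual scores are kept in retrievable form. The article does not say whether each score enters the database.
- *Listed events of grade 3 or 4, or serious.* Adverse events count from the first dose with no stability condition. Grades 3 and 4 go into the case report form and database, and serious events are reported to the principal investigator.
- *Listed events of grade 1 or 2 that are not serious.* The section *Adverse event recording* says these grades are not recorded. The end point sets no grade threshold, so an early mild cranial nerve palsy or cerebellar symptom would meet the end-point definition and might be captured nowhere.

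**5. Number affected.** This would need a rate of neurologic events, their timing and their grade. The article gives none of these, so no count can be derived.

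**The case against.** The strongest reply is that the end point has only one definition. It stands under *End points*, the analysis text uses that end point's name and adds no 7-day condition, and the monitoring entry is a list of things to watch for. Nothing says that the monitoring entry overrides the end point or limits what is recorded. Daily inpatient GCS, the 14-day admission, and adverse event recording from the first dose mean that most early events can be reconstructed whatever the monitoring wording says. The case report form is not shown and may already follow the end-point definition.

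Much of this stands. A reader might infer that early events are simply lost, or that nothing in the first week can count. The documents do not support that: recoverable events are not lost, and the stability clause may not reach focal signs. A reader might also infer that the hazard ratio is biased. That is not supported either. The trial is double-blind, so any under-flagging follows the same rule in both arms, which makes capture that differs by arm unlikely. Moving to the later-starting definition would change what is estimated, which is not the same as biasing it.

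The reply does not remove the contradiction. The same event is defined twice with different results, no text reconciles the two, and the other data sources leave a gap at the lower grades.

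**Conclusion.** The point holds as an unreconciled contradiction in the event definition of "Time to new neurologic event or death until 10 weeks". Its certain size is that the monitoring wording closes at least 10% of the window to GCS events, and all of it for a patient who never stabilises. Its clearest practical consequence is narrower: listed events below grade 3 and not otherwise serious, early in follow-up, may go unrecorded. How many there are cannot be worked out from the article.

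This rests on two assumptions: that sites may flag events by the monitoring wording, and that daily inpatient scores can be retrieved. If the case report form already captures every listed event from randomisation, only the text needs correcting. If daily scores cannot be retrieved, early GCS falls join the gap.

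One secondary end point is affected. The primary end point of 10-week survival and the sample size are not.

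**What to change.** Use the definition in the end-point section for both capture and analysis:

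1. In the outcome-monitoring text of *Clinical monitoring*, remove the condition of more than 7 days' stability and refer to the end-point definition, including its reference score and full event list.
2. In the case report form guidance, have sites record every listed neurologic event with its date from randomisation, whatever its grade, as an exception to the rule that grades 1 and 2 are not recorded.
3. For patients already enrolled, derive GCS events from the daily inpatient records before unblinding, and report any listed low-grade events that cannot be recovered as a limitation.

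The change concerns outcome recording only and does not alter patient care. It costs a short protocol and guidance correction, a small addition to recording for the named events, and retrieval of inpatient GCS where scores are not already entered. *Trial status* gives 417 of 880 patients recruited by 6 August 2014, so 880 − 417 = 463 were still to be enrolled and could be covered prospectively. The study statistician remains blinded throughout, so the definition can be settled without knowledge of results by arm.

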**Table 5 Tab5:** **Presumptive and definitive criteria for AIDS-defining events**

	Presumptive criteria	Definitive criteria
**Constitutional disease**		
HIV wasting syndrome	Unexplained involuntary weight loss >10% from baseline PLUS persistent diarrhoea with ≥2 liquid stools/day for >1 month OR chronic weakness OR persistent fever >1 month. Should exclude other causes such as cancer, TB, MAC, cryptosporidiosis or other specific enteritis	
